### Screening assessment and group allocation

We will screen participants during a telephone call (and only invite them to participate in the study if deemed eligible). Those who will meet inclusion criteria will be randomly assigned to the experimental group or the control group. The experimental group will downregulate activity in the hippocampus; the control group will downregulate activity in the intraparietal sulcus, a region that plays a key role in spatial attention [15] but not in pattern separation or memory. The participants will not be informed which area they will need to regulate (i.e., from which area they will receive feedback). Thus, we will apply a single-blind, randomized, parallel-group design. Choosing an alternative region in a control group will ensure physiological specificity to ensure that only the regulation of hippocampal activity (and not the regulation of any other brain region) will lead to a reduction of hippocampal hyperactivity and, in consequence, to an improvement in memory performance [16]. Group allocation will be conducted by the Clinical Trials Unit Bern with computer-generated random numbers, stratified for age, gender, and group status (i.e., MCI or healthy volunteers).

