### Pattern separation task

We chose to apply a pattern separation task, as hippocampal hyperactivity has been found particularly with this task in patients with MCI [7, 8]. The pattern separation task will be presented with PsychoPy (version 3.1 [21];). All participants will complete two runs of an explicit version of the task [22], during which coloured pictures of objects will be presented. These objects can be new (first presentations), repetitions of previously shown objects (repetitions), objects similar to those previously shown (lures), or new objects presented only once (foils; Fig. 2). Participants will need to categorize each object as either new, old, or similar. One run will include 200 stimuli, and each stimulus will be presented for 2 s with 0.5 s inter-stimulus interval. The 200 stimuli will include 40 foils, 40 repetitions, and 40 lures with an additional 40 of first presentations for repetitions and lures, respectively. The order of object presentation will be randomized for each participant. As in previous studies, the contrast of interest for the definition of baseline hippocampal activity will be lures > foils [7].

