### Statistical analyses

The primary outcome is the change in hippocampal activity as assessed with a pattern separation task during fMRI before and after both neurofeedback sessions. For the determination of intervention effects on hippocampal activity, we will compute repeated measures ANOVA with intervention (experimental vs. control group) and group (healthy volunteers vs. patients with MCI due to AD) as between-subject factors. We will include the genetic variants of ApoE and BDNF as covariates. Next, we are planning to compute regression analyses since we hypothesize that the reduction of hippocampal activity will be associated with memory performance change in the pattern separation task and the VLMT. As exploratory analyses, we will investigate whether any variable predicts successful neurofeedback; we will calculate the association between Aβ levels in blood and hippocampal activity; and we will identify the most successful downregulation strategies. For the prediction of successful neurofeedback, we will apply machine learning methods (e.g., cross-validated non-linear multivariate classification) to obtain the most important features.

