### Data management

All data will be entered by the study team and stored using Research Electronic Data Capture (REDCap), hosted by the Clinical Trials Unit (CTU) Bern. The study team is responsible for data management; data monitoring will be done by an independent researcher not involved in the study. We will record any spontaneously reported adverse events or other unintended effects of the intervention. An annual safety report will be submitted once a year to the local Ethics Committee. Study data will be stored on servers of Bern University, stripped of personal information of the participants. Unblinding will occur after all raw data have been transferred to the data analysis software. All computers will be password-protected and encrypted. At the end of the study, all personal data will be deleted. The procedures comply with Swiss data privacy laws.

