Since we will gather blood samples to assess Aβ levels, we may also be able to replicate previous research in healthy elderly individuals, or patients with MCI, that reported higher levels of Aβ are associated with increased hippocampal activity [7, 9]. We will extend prior research by testing whether this association is also evident using blood-derived Aβ levels. In addition, blood samples will be used for the determination of the genetic variants of ApoE and BDNF. This will allow an exploration of the association of gene status with hippocampal hyperactivity, the ability to downregulate via neurofeedback, and the improvement in memory performance. Besides the primary goal of reducing hippocampal hyperactivity, we may also provide information as to whether successful neurofeedback can be predicted by variables extracted from questionnaires [27]. We expect that participants who score high on mental imagery as well as self-efficiency would benefit from the intervention. Likewise, those with high scores on openness and low scores on state/trait anxiety may be those who learn fast from feedback.

One limiting factor of our study might be the single-blind design. We will not inform the participants from which area they will receive feedback; yet, investigators will need to generate the ROI files and prepare the individual neurofeedback setup. Thus, they will not be blinded. In future studies, a double-blind protocol that could be implemented by separating investigators whot prepare the individual setup from investigators who instruct the participants would be desirable.

In sum, our study will provide insight into the efficacy of real-time fMRI neurofeedback to downregulate hippocampal hyperactivity in patients with MCI due to AD. It will further elucidate whether downregulation will lead to memory improvement. Data extracted from questionnaires may help to identify factors that predict successful neurofeedback.

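### The stated unblinding point, transfer of raw data to the analysis software, allows the primary fMRI outcome to be derived with the arm known, and the plan does not say whose blind ends there

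*Protocol article*

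**What the plan says.** Under Data management, the protocol article gives its only unblinding rule: "Unblinding will occur after all raw data have been transferred to the data analysis software". The same section assigns responsibility: "The study team is responsible for data management; data monitoring will be done by an independent researcher not involved in the study". No data analyst is named, masked or otherwise.

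On who is blinded, Screening assessment and group allocation says "The participants will not be informed which area they will need to regulate", and concludes "Thus, we will apply a single-blind, randomized, parallel-group design". The Discussion lists the single-blind design as a limitation, because "investigators will need to generate the ROI files and prepare the individual neurofeedback setup. Thus, they will not be blinded".

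On the outcome, Statistical analyses says "The primary outcome is the change in hippocampal activity as assessed with a pattern separation task during fMRI before and after both neurofeedback sessions". Under Pattern separation task, "the contrast of interest for the definition of baseline hippocampal activity will be lures > foils". Neurofeedback setup defines the feedback regions as individual anatomical masks made with FreeSurfer from the baseline T1 images.

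**The concern.** For a questionnaire total or a laboratory value, the raw data are close to the outcome, and unblinding once they are in the analysis software does little harm. Task fMRI is different. Someone must decide which scans or participants fail for motion or quality, how the images are preprocessed, how the first-level model is specified, and how the hippocampal value is extracted. All of this comes after the raw data exist, and each decision can move a participant's value.

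The people who run the neurofeedback cannot be masked, as the authors concede. Masked derivation of the outcome is feasible, and it is the main protection left against bias after data collection. A trigger set at raw-data transfer does not secure it. The rule also leaves open whom it covers. Participants have no part in loading data into software, so the wording suggests a masked analyst, but the article identifies none.

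**Working it through.** **Order of events**

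1. Raw data go into the analysis software (Data management).
2. From that point unblinding is permitted (same sentence).
3. The primary outcome is a change in hippocampal activity (Statistical analyses). Baseline MRI collects 1,080 EPI volumes during the task, and the task is repeated after the intervention. Exclusions, preprocessing, first-level modelling and extraction stand between those volumes and one number per participant and session.
4. No sentence requires step 3 to be finished before unblinding. Arm-aware derivation is therefore allowed, but not prescribed.

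**Who could be masked**

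- Participants: blinded to the target region.
- Investigators who prepare the regions and setup: not blinded at any stage (Discussion).
- Whoever processes the scans: not stated.

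Baseline and post-intervention scans use the same task in both arms, with different objects at the second scan. By design, then, the scans should not reveal the arm once they are re-coded. Allocation knowledge would come from the key or from the neurofeedback setup files.

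**The plan's own figure, for context**

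Sample size calculation gives f = 0.25, alpha = 0.01, power 0.99, 4 groups, 4 measurements and N = 84. Taking a correlation of 0.5 between measurements and no sphericity correction (neither is stated):

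- lambda = f² × N × m / (1 − rho) = 0.0625 × 84 × 4 / 0.5 = 42
- df = (4 − 1)(4 − 1) = 9 and (84 − 4)(4 − 1) = 240
- power = 0.992, and 84 is the smallest multiple of 4 that reaches 0.99

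The figure reproduces, and the timing of unblinding does not alter it.

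**Illustration of leverage**

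Inputs: 21 per cell (Sample size calculation); 2 × 21 = 42 per arm with MCI and healthy volunteers pooled. Assumed, not from the document: k participants excluded, each 1.5 SD of the change score on the unfavourable side.

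Shift of the mean = 1.5k / (n − k):

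- k = 1: cell 1.5/20 = 0.075 SD; arm 1.5/41 = 0.037 SD
- k = 2: cell 3.0/19 = 0.158 SD; arm 3.0/40 = 0.075 SD
- k = 3: cell 4.5/18 = 0.250 SD; arm 4.5/39 = 0.115 SD

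Yardstick: in a two-arm pre-post comparison, a difference in change d puts each of the four arm-by-time means d/4 from additivity. So f = d/(4 SD), and f = 0.25 gives d = 4 × 0.25 = 1.0 SD of a single measurement. The SD of a change score is √(2(1 − rho)) times that SD, which is 1 at rho = 0.5. For k = 2 the shift is then about 16% of d within one cell and 7.5% for a pooled arm.

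With rho = 0.3 the factor is √1.4 = 1.183, giving 0.187 and 0.089 SD. With rho = 0.7 it is √0.6 = 0.775, giving 0.122 and 0.058 SD.

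**The case against.** The strongest case on the other side has five parts.

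- **The sentence says after transfer, not on transfer.** A reader might infer that the arm is known during preprocessing and exclusions. The document does not say so, and a fuller protocol or analysis plan could require masked processing. This stands, and it is why the point is about what the rule allows. It does not remove the point, because the article states a milestone and places it before the step that needs protection.
- **The software meant may be the statistics package, with participant-level values already derived.** The sentence sits beside text on database entry and does not mention scans. This is possible, but the sentence speaks of raw data and says nothing of derived values. If this is what was meant, one clause would settle it.
- **The Discussion already discloses the unblinded investigators.** This stands. A reader might infer that the two sections contradict each other, or that the rule protects nobody. Neither is shown: participants, or a separate analyst, could still be blind until the stated point. What is missing is whose blind it is.
- **Some choices are fixed in advance.** The contrast is set, although only for baseline activity, and anatomical masks are set, although only for neurofeedback. This narrows the open choices but does not cover exclusions, preprocessing or model specification.
- **Re-coding cannot re-blind someone who prepared a participant's setup.** This stands in part. Masking works only if the person processing the scans has neither the key nor the setup files.

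**Conclusion.** The point holds in a limited form. The one stated unblinding trigger comes before derivation of the primary outcome and does not say whose blind it ends, so it permits arm-aware processing. It does not show that such processing is planned or that bias will occur. This is a recommended correction: it concerns freedom from bias in the primary analysis and is cheap to make.

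The size is illustrative only. It rests on assumed exclusions (two participants at 1.5 SD), a correlation of 0.5, and the translation of the planned f from four groups and four measurements to a two-arm pre-post comparison. A reader might obtain a more alarming proportion by setting the one-cell shift against an effect smaller than the planned one. The document gives only f = 0.25, and its intervention factor pools the two participant groups, so the smaller, pooled figure is the relevant one for that comparison. The conclusion does not depend on either figure.

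**What to change.** Replace the trigger under Data management. Allocation is released to the analysis only after these are locked for all participants: the hippocampal lures > foils estimate for each session, the quality exclusions, and the memory scores. To make this workable:

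- Re-code the baseline and post-intervention scans before processing, with the key held by the Clinical Trials Unit, which already performs the allocation.
- Assign processing and extraction to a team member who has no access to the key or to the neurofeedback setup files.
- State in the same section whose blind is broken at release, in terms consistent with the Discussion's account of the unblinded setup investigators.

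The cost is a change of wording, a re-coding step and the assignment of an existing team member to masked processing. Sample size, visits and procedures for participants do not change. If setup staff must also process scans, masking will be incomplete, and the plan should say so.

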## Discussion

This study will examine whether real-time fMRI neurofeedback can reduce hippocampal hyperactivity and whether the reduction will lead to an improvement in memory performance. This will extend former research showing that a pharmacological reduction of excess hippocampal activity in patients with MCI led to better memory performance using a pattern separation task [7]. In contrast to medication, real-time fMRI neurofeedback comes with considerably fewer risks or side effects [33]. In addition, it may give patients a sense of empowerment as they themselves tone down hyperactivity without having to ‘depend on’ taking medication. So far, the assessment of the effectiveness of downregulating the hippocampus requires using a set-up including an MR scanner. This study may provide insight into strategies that participants have successfully used to regulate hippocampal activity. It would be such strategies that may be included in future cognitive intervention studies. Should our study be successful, we will test whether other participants could use such strategies for themselves or whether each person will need to develop their own strategy. In the context of clinical use, only a few training sessions may produce long lasting effects [34, 35].

One aspect that may likely influence our results is the type of control group [28]. We opted for an active control rather than no feedback or yoked feedback; that is, feedback is given on the activity of a control region. In our view, only the comparison with an active control group can confirm that the results are specific to feedback from hippocampal activity [16]. However, differences between groups might still be related to differences in the perceived difficulty to regulate. We will account for this by evaluating how difficult participants thought it was to regulate.

Since we will gather blood samples to assess Aβ levels, we may also be able to replicate previous research in healthy elderly individuals, or patients with MCI, that reported higher levels of Aβ are associated with increased hippocampal activity [7, 9]. We will extend prior research by testing whether this association is also evident using blood-derived Aβ levels. In addition, blood samples will be used for the determination of the genetic variants of ApoE and BDNF. This will allow an exploration of the association of gene status with hippocampal hyperactivity, the ability to downregulate via neurofeedback, and the improvement in memory performance. Besides the primary goal of reducing hippocampal hyperactivity, we may also provide information as to whether successful neurofeedback can be predicted by variables extracted from questionnaires [27]. We expect that participants who score high on mental imagery as well as self-efficiency would benefit from the intervention. Likewise, those with high scores on openness and low scores on state/trait anxiety may be those who learn fast from feedback.

One limiting factor of our study might be the single-blind design. We will not inform the participants from which area they will receive feedback; yet, investigators will need to generate the ROI files and prepare the individual neurofeedback setup. Thus, they will not be blinded. In future studies, a double-blind protocol that could be implemented by separating investigators whot prepare the individual setup from investigators who instruct the participants would be desirable.

In sum, our study will provide insight into the efficacy of real-time fMRI neurofeedback to downregulate hippocampal hyperactivity in patients with MCI due to AD. It will further elucidate whether downregulation will lead to memory improvement. Data extracted from questionnaires may help to identify factors that predict successful neurofeedback.

## Data Availability

All data generated and/or analysed during the study will be made available from the corresponding author on request.

## Abbreviations

AD: Alzheimer’s disease
ANOVA: Analysis of Variance
ApoE: Apolipoprotein E
Aβ: Amyloid beta
BDNF: Brain derived neurotrophic factor
CERAD: Consortium to Establish a Registry for Alzheimer’s Disease
CFD: Cognitive Functions Dementia
CTU: Clinical Trials Unit
EPI: Echo Planar Imaging
fMRI: Functional magnetic resonance imaging
GDS: Geriatric Depression Scale
iGLM: Incremental general linear model
MCI: Mild Cognitive Impairment
MoCA: Montreal Cognitive Assessment
MP2RAGE: Magnetization-Prepared 2 Rapid Acquisition Gradient Echoes
PANAS: Positive and Negative Affect Schedule
POMS: Profile of mood states
PSC: Percent signal change
ROI: Region of interest
VLMT: Verbal Learning and Memory Task
